# The INCH-Trial: a multicentre randomized controlled trial comparing the efficacy of conventional open surgery and laparoscopic surgery for incisional hernia repair

**DOI:** 10.1186/1471-2482-13-18

**Published:** 2013-06-07

## Abstract

**Background:**

Annually approximately 100.000 patients undergo a laparotomy in the Netherlands. About 15,000 of these patients will develop an incisional hernia. Both open and laparoscopic surgical repair have been proven to be safe. However, the most effective treatment of incisional hernias remains unclear. This study, the ‘INCH-trial’, comparing cost-effectiveness of open and laparoscopic incisional hernia repair, is therefore needed.

**Methods/Design:**

A randomized multi-center clinical trial comparing cost-effectiveness of open and laparoscopic repair of incisional hernias. Patients with a symptomatic incisional hernia, eligible for laparoscopic and open incisional hernia repair. Only surgeons, experienced in both open and laparoscopic incisional hernia repair, will participate in the INCH trial. During incisional hernia repair, a mesh is placed under or on top of the fascia, with a minimal overlap of 5 cm. Primary endpoint is length of hospital stay after an incisional hernia repair. Secondary endpoints are time to full recovery within three months after index surgery, post-operative complications, recurrences, mortality and quality of life.

Our hypothesis is that laparoscopic incisional hernia repair comes with a significant shorter hospital stay compared to open incisional hernia repair. A difference of two days is considered significant. One-hunderd-and-thirty-five patients are enrolled in each treatment arm. The economic evaluation will be performed from a societal perspective. Primary outcomes are costs per patient related to time-to-recovery and quality of life.

The main goal of the trial is to establish whether laparoscopic incisional hernia repair is superior to conventional open incisional hernia repair in terms of cost-effectiveness. This is measured through length of hospital stay and quality of life. Secondary endpoints are re-operation rate due to post-operative complications or recurrences, mortality and quality of life.

**Discussion:**

The difference in time to full recovery between the two treatment strategies is thought to be in favor of laparoscopic incisional hernia repair. Laparoscopic incisional hernia repair is therefore expected to be a more cost-effective approach.

**Trial registration:**

Netherlands Trial register: NTR2808

## Background

Incisional hernias are defects of the fascia of the abdominal wall, covered by skin, which can develop after abdominal surgery. Bulging through the scar is visible and palpable when patients are standing or coughing
[1,2]. These hernias occur in at least 15% of patients after open abdominal surgery within ten years after surgery. Incisional hernias may be asymptomatic, but frequently they cause pain and give aesthetic complaints. They can also cause serious complications like strangulation of the bowel. The quality of life in these patients as well as their chances for employment is reduced
[2].

Pre-disposing factors to get an incisional hernia are obesity, which is increasing rapidly in the Western world, and a post-operative surgical site infection
[3]. There are no differences between men and women in developing an incisional hernia. Ethnical differences are not known. The pathogenesis of incisional hernias is complex; altered collagen metabolism and extra-cellular matrix disorders causing wound-healing disorders have been found in patients who developed incisional hernias
[4].

A population based study showed a 3,7% yearly increase in the incidence of incisional hernia repair per 10.000 people
[5] in the United States. Since obesity plays an important role in developing an incisional hernia and is an increasing problem in the Netherlands, we expect the incidence of incisional hernias to increase in the Netherlands as well. Mean age at time of the surgical repair is 58 years old, mean SD 15 years
[6]. The majority of these patients will have to go back to work.

Eighty percent of the patients with an incisional hernia undergo surgical repair
[5]. The morbidity of open incisional hernia repair is more than 20% involving recurrence and mesh infection. Laparoscopic surgery tends to be safe and is associated with less infections and shorter hospitalization. It is highly feasible in obese patients, because of a good exposure of the incisional hernia. However, the surgical procedure can be difficult and the operating time might be longer. Up till now it is not clear what is the best treatment strategy for incisional hernias. The potential benefits of a more defined treatment strategy includes a shorter hospital admission, cost reduction and less post-operative complications.

Two recent meta-analysis
[7,8] state that laparoscopic repair is at least as effective and might be superior to the open approach in a number of outcomes. Total hospital stay was shorter and less post-operative complications were seen. The largest study in the meta-analysis
[8] has several shortcomings; randomization is not listed and there was no sample size calculation. Most studies only provide short-term follow-up evaluation and cost-effectiveness is not evaluated. This study, comparing the cost-effectiveness of open and laparoscopic incisional hernia repair, is therefore needed.

Criteria to recommend a surgical repair should be stated and the natural course of an incisional hernia should be examined.

This is a multi-centre study with surgeons who are experienced in open as well as laparoscopic surgery. The study group exists of dedicated laparoscopic surgeons, committed to improve hernia-care. First, we want to know if laparoscopic repair is more effective than open repair. The future of this study will allow evidence-based change of practice.

## Methods/Design

A randomized multi-centre trial comparing the cost-effectiveness of two surgical techniques for the repair of incisional hernias: laparoscopic vs. conventional open repair.

### Inclusion criteria

The following patients will be eligible for the randomization to either open or laparoscopic repair: Adult patients who are referred to the surgical clinic for assessment of an incisional hernia, either primary or recurrent. Imaging of the abdomen will only be done when it is unclear whether an incisional hernia is present. The need for surgery will be determined; pain, severe discomfort and episodes of visceral incarceration are indications for surgery. Only symptomatic patients will get a surgical correction of the incisional hernia. Patients whose incisional hernia is suitable for laparoscopic repair are included in the trial, this decision is at the discretion of the surgeon. After consenting to the study, the patient will be randomized to either open or laparoscopic repair. Patients who are excluded or who don’t want to participate will be registered. (Figure 
1; flowchart).

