### Case record form

*At first presentation* in the outpatient clinics: age/sex/co-morbidity/pre-illness/working-social activities/surgical history/symptoms of the incisional hernia/classification of the incisional hernia:

The European Hernia Society (EHS) tried to categorize incisional hernias, in order to be able to compare different scientific incisional hernia research
[10]. A classification system of abdominal wall hernias was formulated (Figure 
2). This classification will be used in the INCH-trial.

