### Analysis of cost-effectiveness

The analysis will be done according to the intention-to-treat principle. Missing cost and effect data will be imputed using multiple imputations according to the MICE algorithm developed by Van Buuren
[13]. Costs typically have a highly skewed distribution. Policy makers want to have information on the difference in mean total costs between the two treatment-groups to be able to estimate the total health care budget needed for a specific condition
[14]. Therefore, bias-corrected and accelerated bootstrapping with 5000 replications will be used to calculate 95% confidence intervals around the mean difference in total costs between the treatment groups. Incremental cost-effectiveness ratios (ICERs) will be calculated by dividing the difference in mean total costs between the treatment groups by the difference in mean effects between the treatment groups. Bootstrapping will be used to estimate the uncertainty surrounding the ICERs, which will be graphically presented on cost-effectiveness planes. Cost-effectiveness acceptability curves and net monetary benefits will also be calculated. Cost-effectiveness acceptability curves show the probability that collaborative care is cost-effective in comparison with usual care for a range of different ceiling ratios thereby showing decision uncertainty
[15].

The baseline data of both treatment groups will be described and 95% confidence intervals will be calculated. Additional as-treated analyses will be done, because patients who were planned to have a laparoscopic repair might have had an open correction and vice versa. Differences in primary and secondary endpoints between the two treatment groups will be calculated as well as their 95% confidence intervals. Student’s t tests, Chi square tests or Fisher exact tests will be applied where appropriate. The risk of re-operation will also be studied by application of a multiple logistic regression model.

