### Statistics

*Sample size calculation*: This is a superiority design: Our hypothesis is that length of hospital stay is shorter after incisional hernia repair, and therefore the laparoscopic approach will be superior in terms of cost-effectiveness. Statistics are based on an average hospital stay of 2 days (SD 5) after laparoscopic repair
[8]. The outcome is considered superior if there is a difference in hospital stay of more than 2 days. Therefore, 135 patients in each treatment arm are needed (alpha 0,05/power 0,9)
[16]. Loss to follow-up may occur; we will therefore aim for an inclusion of 300 patients.

*Randomisation* will be performed through a computer-guided system. A stratified block-randomisation will be used per centre. The randomisation code will be noted on the patients file. Peritonitis carcinomatosa, unplanned surgical procedures for pathology that was not discovered during pre-operative analysis, absence of an incisional hernia are reasons for post-randomization exclusion.

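### The length-of-stay comparison is planned as an unadjusted test, although hernia class and surgical history are recorded before randomisation and centre is a stratum: precision is left unused, but the comparison is valid

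*Protocol article*

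**What the plan says.** Under Inclusion criteria, the protocol article takes "Adult patients who are referred to the surgical clinic for assessment of an incisional hernia, either primary or recurrent". It gives no numerical size limit but does apply a filter: "Patients whose incisional hernia is suitable for laparoscopic repair are included in the trial, this decision is at the discretion of the surgeon". Randomisation follows consent.

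Under Case record form, the items collected at first presentation in the outpatient clinic include "surgical history/symptoms of the incisional hernia/classification of the incisional hernia". Of the European Hernia Society (EHS) scheme it says "This classification will be used in the INCH-trial".

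Under Statistics, the only stratification factor named is centre: "A stratified block-randomisation will be used per centre".

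Under Analysis of cost-effectiveness (second paragraph), "Differences in primary and secondary endpoints between the two treatment groups will be calculated as well as their 95% confidence intervals", and then "Student’s t tests, Chi square tests or Fisher exact tests will be applied where appropriate". The only regression model named is for another endpoint: "The risk of re-operation will also be studied by application of a multiple logistic regression model".

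**The concern.** The article does more than leave the analysis open. It names the tests, which for a continuous outcome such as length of stay means Student's t test, and it keeps multivariable modelling for re-operation. Yet it collects, before allocation, descriptors of the hernia that could plausibly be related to length of stay, and it stratifies by centre without carrying centre into the named analysis.

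If those variables predict stay, leaving them out puts explainable variation into the error term of the primary comparison, and the estimate carries whatever chance difference in case mix arises between the arms. At stake is the width of the confidence interval around the difference in days. Prespecification matters too: if no adjusted analysis is fixed in advance, a later choice between adjusted and unadjusted results could be driven by the data.

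**Working it through.** **Inputs from the protocol article (Statistics, sample size):** difference 2 days; SD 5 (given for the laparoscopic arm with mean 2, taken here as common to both arms); alpha 0.05; power 0.90; 135 per arm.

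**Step 1. Reproduce the plan's figure.** n per arm = 2 × (1.960 + 1.282)² × 5² / 2² = 131.4, so 132. The exact t-test calculation gives 132.3, so 133. The stated 135 agrees to within 3%. Sidedness is not stated; a one-sided alpha would give 108, so the plan's figure is two-sided.

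**Step 2. Unadjusted precision and power at 135 per arm.** SE = 5 × √(2/135) = 0.609 days. Power = Φ(2/0.609 − 1.96) = 90.8%. The planned 90% is met without adjustment.

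**Step 3. Effect of adjustment.** If the baseline factors explain a share R² of the variance in stay, the residual SD is 5 × √(1 − R²). The documents give no R², so a range is shown as an assumption.

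| Assumed R² | Residual SD | SE (days) | Fall in SE | Power at 2 days | n per arm for 90% | Equivalent gain in patients, 1/(1 − R²) − 1 |
|---|---|---|---|---|---|---|
| 0 | 5.000 | 0.609 | – | 90.8% | 132 | – |
| 0.05 | 4.873 | 0.593 | 3% | 92.1% | 125 | 5% |
| 0.10 | 4.743 | 0.577 | 5% | 93.4% | 119 | 11% |
| 0.20 | 4.472 | 0.544 | 11% | 95.7% | 106 | 25% |

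**Step 4. Chance imbalance in days.** Suppose 30% of hernias are recurrent (assumption).

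- The between-arm difference in that share has SD √(2 × 0.3 × 0.7/135) = 0.0558, or 5.6 percentage points. A difference of 10 points or more has two-sided probability of about 0.07.
- If recurrence adds 2 days to stay (assumption), the resulting shift in the estimate has SD 2 × 0.0558 = 0.11 days, with 95% of trials within ±0.22.
- If it adds 4 days (assumption), the SD is 0.22 days, with 95% within ±0.44.

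These shifts are part of the 0.609-day SE in Step 2 and do not come on top of it. In the 2-day case the factor contributes 2² × 0.3 × 0.7 = 0.84 of a variance of 25, an R² of about 3%.

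**Step 5. Which end of the range?** Stay cannot be negative, so a mean of 2 with an SD of 5 (2.5 times the mean) implies strong right skew. A few very long stays may dominate the variance, and hernia class may explain little of it. Imaging is reserved for doubtful diagnoses (Inclusion criteria), so class at first presentation will often be a clinical estimate. Both points favour the lower rows of R².

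**The case against.** The strongest case against is that nothing is wrong. This is a condensed article, the covariate list is commonly left to an analysis plan that is not shown, and the wording on tests does not exclude adjustment. Power is already met, and every driver of the gain is assumed: the share of recurrent hernias, their effect on stay, and R². The EHS content is in a figure that is not shown, so the documents cannot confirm that the class captures size. Entry is also narrower than it first looks, given the suitability filter and the exclusions for ostomy, previous open-abdomen treatment, immune compromise and ASA above 3.

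Most of this stands and limits the point to a recommendation. The reply on scope is that the article does state an analysis. The qualifier on the tests reads most naturally as a choice among three unadjusted tests, and regression is named only for re-operation. An unseen analysis plan may already add adjustment; if so, the point is met.

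A reader might go further and infer that chance imbalance is left uncorrected and distorts the result, the more so because the trial is unblinded. The documents do not support that. Under randomisation, chance imbalance is random error already covered by the 5% alpha and the 95% CI, and lack of blinding has no bearing on it. Nor would adjustment remove all such imbalance; it removes only the part that the recorded variables explain.

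**Conclusion.** The point holds as an efficiency improvement. On the article's text, the length-of-stay comparison uses neither the hernia characteristics recorded before randomisation nor the stratification factor. The unadjusted comparison is valid and the sample size stands.

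The gain is modest: for assumed R² of 5–20%, power at 2 days goes from 90.8% to about 92–96% and the SE falls by about 3–11%, with the low end the more likely given the skew. It rests on an SD of 5 in both arms, a two-sided alpha of 0.05, 135 analysed per arm, and an R² that the documents do not supply. No gain from centre is counted in these figures; centre belongs in the model because randomisation was stratified by it.

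**What to change.** Keep the entry criteria and the centre-stratified randomisation. In Analysis of cost-effectiveness, state that the primary difference in mean days of stay and its 95% CI come from a prespecified linear model with treatment, centre, EHS class and primary or recurrent status, all as recorded before randomisation. Use robust or bootstrap standard errors because stay is skewed, and report the unadjusted difference as a sensitivity analysis.

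Fix in advance how EHS class is grouped, how small centres are handled and what is done with missing values. Confirm that primary or recurrent status is a field on the form or can be read from surgical history.

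Do not adjust for defect size seen at operation: it is observed after allocation, and the defect photograph described under Treatment is specified for laparoscopic surgery only.

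The cost is one sentence in the analysis text plus these coding rules, with no extra patients or procedures. Classification and surgical history are already on the case record form.

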**Figure 1 F1:**
[figure not shown]
Flowchart.

### Exclusion criteria

1. Pregnancy

2. Age less than 18 years old 18

3. Abdominal ostomy

4. History of open abdomen treatment

5. Mentally or cognitively unable to be consented

6. A life expectancy of less than one year

7. Immune-compromised patients

8. ASA > 3 (ASA: scoring system of the American Society of Anaesthesiologists)

### Treatment

Patients will be randomized, using a computer-program, to one of the following surgical approaches:

I) **Open repair** of the incisional hernia: the employed open technique is at the discretion of the participating surgeon. There is no evidence, which open technique, is best; bridging as well as augmenting techniques might be used. Onlay, sublay as well as CST technique are allowed as long as a mesh is used. An overlap of at least 5 cm of the mesh over the fascia is preferable.

II) **Laparoscopic repair** of incisional hernias will entail employment of mesh that is placed subfascially with a minimal overlap of 5 cm. Choice and fixation of the mesh is at the discretion of the surgical team. During laparoscopic surgery a photograph will be taken of the hernia defect before and after the correction is done. When laparoscopic repair is not successfully achieved or complications occur, the surgeon may decide to change to the open surgical procedure (i.e. conversion); this is common practice in laparoscopic surgery.

In each approach, the use of a mesh is preferable, as this has shown to reduce the recurrence-rate
[9]. Every detail of the technique should be described. Dutch hernia experts will perform the surgical corrections.

### Case record form

*At first presentation* in the outpatient clinics: age/sex/co-morbidity/pre-illness/working-social activities/surgical history/symptoms of the incisional hernia/classification of the incisional hernia:

The European Hernia Society (EHS) tried to categorize incisional hernias, in order to be able to compare different scientific incisional hernia research
[10]. A classification system of abdominal wall hernias was formulated (Figure 
2). This classification will be used in the INCH-trial.

**Figure 2 F2:**
[figure not shown]
Classification of incisional hernias according tot the European Hernia Society.

Postoperatively: open or laparoscopic/length of the scar/duration of surgery/type of mesh used/size of the mesh/type of mesh fixation/presence of bleeding/accidental bowel lesion/use of tubes/use of per-operative antibiotics/possible re-operation.

Inpatient: daily VAS score/use of analgesics/length of hospital stay/morbidity/mortality/QOL at two days post-surgery.

During Follow-up at 2 weeks and 3 months: healthcare and lost productivity costs/QOL at 2 weeks and 3 months post-surgery will be measured through the Short Form 36 and the Carolina Comfort Scale/time to return to work/recurrence/pain/wound infection/patient satisfaction/other morbidity.

During long-term follow-up at 1, 3 and 5 years: Recurrence/pain/wound infection/patient satisfaction/other morbidity.

**Primary outcomes** are:

Length of hospital stay. This is the time until discharge. A patient can be discharged when he/she is able to move normally, tolerate a normal diet and has a VAS painscore < 5 without the use of opiates.

Quality of life measures through SF-36 and CCS.

**Secondary endpoints** are:

Re-operation rate for recurrence or complications of the incisional hernia repair. The analysis will be continued after the cost-effectiveness study has ended, a longer follow-up is needed to examine the recurrence-rate.

28 days post surgery morbidity and mortality,

Total mean costs will be related to the following effect measures in the cost-effectiveness analyses:

1) Time to full recovery.

2) Quality-adjusted life-years (QALYs) based on the SF-36D
[11].

Intention to treat analysis will be performed. Blinding is impossible as the surgical difference is visible from the outside.

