### Goal

The goal of the trial is to establish whether laparoscopic incisional hernia repair is superior to conventional open incisional hernia repair in terms of cost-effectiveness. This is measured through length of hospital stay and quality of life. Secondary endpoints are re-operation-rate (due to complications or recurrence), morbidity, mortality and shape of the abdomen.

In current surgical practice there is on going discussion about the possible benefits of laparoscopic incisional hernia surgery. Scientific evidence is lacking to determine whether laparoscopic correction is superior to conventional open techniques in terms of cost-effectiveness.

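### Quality of life is ranked both primary and secondary, while alpha, power and sample size are fixed for length of hospital stay alone

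*Protocol article*

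**What the plan says.** The endpoint is ranked in three places, and they do not agree.

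- **Abstract, Methods/Design.** There is one primary endpoint: "Primary endpoint is length of hospital stay after an incisional hernia repair". Quality of life is then listed as secondary twice, first in "Secondary endpoints are time to full recovery within three months after index surgery, post-operative complications, recurrences, mortality and quality of life" and again in "Secondary endpoints are re-operation rate due to post-operative complications or recurrences, mortality and quality of life". The economic evaluation has its own headline outcomes: "Primary outcomes are costs per patient related to time-to-recovery and quality of life".
- **Case record form, primary outcomes.** Two items are listed. The first is "Length of hospital stay. This is the time until discharge" and the second is "Quality of life measures through SF-36 and CCS". Quality of life does not appear in the secondary list that follows, except through QALYs in the cost-effectiveness analyses.
- **Goal (and the matching paragraph of the Abstract).** The aim is superiority in cost-effectiveness, and "This is measured through length of hospital stay and quality of life". The secondary list in Goal omits quality of life and adds the shape of the abdomen, which no other list contains.

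The Statistics section works with length of stay alone. It takes a difference of 2 days, SD 5, alpha 0.05 and power 0.9, arrives at 135 per arm, and ties the word superior to a difference in stay of more than 2 days. It gives no target difference or SD for quality of life, and no section names a primary scale or time point for it.

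**The concern.** Which endpoint is primary decides what the single 5% error rate and the 90% power refer to. As written, suppose the trial finds no difference in stay but a favourable SF-36 or CCS score. Under the Case record form section that is a result on a primary outcome; under the Abstract it is a secondary finding. The protocol article supports both reports, and the choice could be made after the data are seen.

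The stated operating characteristics hold only if stay stands alone. If quality of life is a second primary, one of two things follows. Either one success is enough, and the overall false-positive rate exceeds 5%; or both must succeed, and the chance of success falls below 90%. The article does not say which applies.

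**Working it through.** **1. The plan's own figure.** Inputs from the Statistics section: difference 2 days, SD 5, alpha 0.05, power 0.9. Sidedness is not stated.

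n per arm = 2 × (z₀.₉₇₅ + z₀.₉₀)² × SD² / difference² = 2 × (1.960 + 1.282)² × 25 / 4 = 131.3, so 132. The t-test version gives 132.3, so 133. The stated 135 is within 3% of this. A one-sided test would need only 108, so the calculation is two-sided.

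Power at 135 per arm: 2 / (5 × √(2/135)) = 3.286; Φ(3.286 − 1.960) = 0.908.

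Allowance for losses: 270 / 0.90 = 300, which matches the planned inclusion.

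The arithmetic is sound for length of stay.

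**2. If any one primary suffices, each at two-sided 5%.** With k independent tests the chance of at least one false positive is 1 − 0.95ᵏ. For correlated tests it comes from equicorrelated normal test statistics. The correlations are assumptions; the document gives none.

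| Primary tests | corr. 0 | 0.3 | 0.5 | 0.7 |
|---|---|---|---|---|
| 2 (stay, one quality-of-life score) | 9.8% | 9.5% | 9.1% | 8.3% |
| 3 (stay, SF-36, CCS) | 14.3% | 13.6% | 12.5% | 10.9% |

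**3. If both must succeed.** Alpha is not inflated. Joint power combines 0.908 for stay with the power for quality of life, which has to be assumed because no target is given.

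| Assumed quality-of-life power | corr. 0 | corr. 0.5 |
|---|---|---|
| 50% | 0.908 × 0.50 = 0.45 | 0.49 |
| 80% | 0.908 × 0.80 = 0.73 | 0.76 |
| 90% | 0.908 × 0.90 = 0.82 | 0.84 |

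Every entry is below 0.90. For orientation, 135 per arm has 90% power for a standardised difference of (1.960 + 1.282) × √(2/135) = 0.39; the document offers no quality-of-life target to set against it.

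**4. What keeping several primaries with a Bonferroni split would cost for stay.**

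| Primaries | Alpha each | n per arm for 90% power | Power at 135 |
|---|---|---|---|
| 1 | 0.05 | 132 | 90.8% |
| 2 | 0.025 | 156 | 85.2% |
| 3 | 0.0167 | 169 | 81.4% |

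Only the first row leaves the planned size adequate.

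**The case against.** The strongest reply is that the article has one explicit superiority criterion, in Statistics, and it concerns stay alone. The stated hypothesis in the Abstract and in Statistics also concerns stay. No sentence says that a quality-of-life result by itself would establish superiority, and Goal joins stay and quality of life with an *and*, which does not read naturally as one-is-enough. An alpha split or testing order is also commonly left to the full protocol or analysis plan, neither of which is shown. All of this stands. It makes the error figures conditional, and it means that the absence of a multiplicity rule is not a separate fault. It does not remove the contradiction, because an analysis plan cannot settle which section of the protocol defines the primary endpoint.

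Two stronger readings are tempting, and the text does not support either.

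- **More tests.** A reader might count both instruments at day 2, 2 weeks and 3 months, which with stay makes seven tests and about 23% at correlation 0.5. The Case record form section names SF-36 and CCS only for 2 weeks and 3 months; its day-2 entry names no instrument. Nor does it say that each visit is a separate primary test.
- **Cost-effectiveness inferred from stay.** A reader might take "therefore the laparoscopic approach will be superior in terms of cost-effectiveness" as a rule that a shorter stay proves cost-effectiveness. The sentence opens as a hypothesis, and no analysis rule follows from it. The economic sections already plan a 3-month societal evaluation with the operation itself costed, incremental cost-effectiveness ratios, bootstrap intervals, acceptability curves and net monetary benefit. That is estimation and does not spend alpha.

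**Conclusion.** The contradiction is real and lies within the article. Quality of life is secondary in the Abstract, primary in the Case record form section, and half of the yardstick in Goal, while the trial is sized, and superiority defined, on stay alone. The sample size is correct for that one endpoint.

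The size of the consequence depends on a rule that the article does not state. Under one-is-enough, the false-positive chance is about 8–10% for two tests or 11–14% for three, for assumed correlations from 0.7 to 0. Under both-must-succeed, joint power is about 0.45–0.84, for an assumed quality-of-life power of 50–90% and correlation 0 to 0.5. These ranges show what is at stake if quality of life is a true second primary; they are not a claim that the trial will run at those rates. The case for correction rests on the contradictory ranking.

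**What to change.** In the Abstract, the Case record form section and Goal, name length of hospital stay as the only primary endpoint, tested at two-sided 5%. List SF-36 and CCS as secondary, and use one identical secondary list in all three places. In Goal, separate the primary comparison (stay) from the cost-effectiveness question. Present the Statistics sentence linking a shorter stay to cost-effectiveness as a hypothesis, to be judged by the economic evaluation already planned.

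This is a wording amendment. It agrees with the Abstract's endpoint statement and with Statistics, and it leaves 135 per arm (300 with losses) unchanged. The price is that quality of life, for which the trial was not sized, can no longer support a primary claim.

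If the sponsor wants a formal quality-of-life claim, a fixed sequence (stay first, then one named score at one named time point) would also hold the 5% level without changing the number of patients. Power for that score would still have to be stated.
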